## Objectives

The primary objective is to assess the feasibility and acceptability of a targeted intervention to improve voices related distress, and social avoidance and distress in people at early stages of psychosis (FEP<5 years^24^). The second main research objective is to convene evidence on clinical outcomes to provide first estimates of efficacy of this enhanced version of AVATAR therapy (AVATAR_VRSocial) in a sample of German individuals with early psychosis, which can inform subsequent development and testing of the therapy. Table 1 summarises the objectives of the study and includes the associated feasibility markers and assessment measures.

**Table 1 T1:** Summary of objectives and related assessment measures

	Objectives	Measures
Primary	Assessing feasibility and acceptability of AVATAR_VR psychotherapy for people who experience distressing voice hearing	Number of patients referred to the study, consented, declined and retainedCompletion rates of each assessment measure and retention at follow-up assessmentsNumber and proportion of consenting participants within AVATAR_VRSocial condition who reach the point of therapy ‘exposure’ (attended at least five of nine therapy sessions)Number of adverse serious and non-serious adverse events in each condition
Secondary	Clinical information about preliminary estimates of clinical effectiveness of AVATAR_VRSocial in addition to treatment as usual vs treatment as usual alone in people in early stages of psychosis	Voice distress, frequency and severity of voices: PSYRATS-AHSocial anxiety and avoidance: O-AS, O-CDQOther voices measures: BAVQ-R; VPDS; Brief assessment of negative hallucinations when outsidePsychiatric symptoms: PSYRATS-DEL, DASS-21. CAINS, Rosenberg-Self-EsteemQuality of life: EQ-5D-5L
Qualitative	Assessing acceptability	AFIMFeedback from Qualitative Interview

AFIM, Acceptability and Feasibility of Intervention Measure; BAVQ-R, Beliefs About Voices Revised; CAINS, Clinical Assessment Interview for Negative Symptoms; DASS21, Depression Anxiety and Stress Scales; EQ-5D-5L, EuroQol BIOMED Research Programme; O-AS, Oxford—Agoraphobic Avoidance Scale; O-CDQ, Oxford Cognitions and Defences Questionnaire; PSYRATS-AH, Psychotic Symptoms Rating Scale—Auditory Hallucinations; PSYRATS-DEL, distress and frequency factors, and total scores on the delusional beliefs subscale of the Psychotic Symptoms Rating Scales; VPDS, Voice Power Differential Scale.

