Participants allocated to the AVATAR_VRSocial Therapy condition will further be asked to complete items regarding anxiety, perceived hostility, sense of presence and sensed presence at the end of each interaction with the avatar (adapted from refs.^39 40^). Following each VR session, participants will be asked to complete a short version of the State Social Paranoia Scale.^41^ Voice activity and content in the past week is monitored at the beginning of each session using select items of the PSYRATS-AH^18^ and the VPDS.^31^ After half of the sessions, participants will be asked to complete a measure of the therapeutic alliance (Working Alliance Inventory-Short Revised).^42^ Before starting the VR sessions, participants will be asked to complete the questionnaires related to social avoidance and social distress. After completion of the final session, participants will rate the acceptability and appropriateness of the therapy via the Acceptability of Intervention Measure and the Intervention Appropriateness Measure.^43^

A qualitative interview will be conducted with a subsample of consecutively recruited participants (n=10). This interview will take place once they have concluded their participation in all assessments in the trial. This interview will ask them for feedback on how they found the therapy, taking part in the trial and the technology/software involved. The interview will be conducted by a research worker or by a member of the Live Experience Advisory Panel with support from the research team.

Assessments and therapy sessions will be audio-recorded (after first establishing consent) to allow for assessment of adherence to the research protocol and assessment ratings. These will be stored securely on password-protected devices and then uploaded to the secure university server. Throughout the recruitment and research process, all efforts will be made to tailor to participants’ needs and preferences. Participants in the study will be reimbursed with a voucher worth €30 in online shopping portals for each baseline, post-therapy and follow-up assessments.

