### Trial interventions

#### AVATAR_VRSocial

AVATAR_VRSocial is an augmented version of the AVATAR therapy (as delivered in Craig *et al*^17^) by adding three additional sessions supported by immersive VR technology. Therefore, this therapy consists of a total of 10 sessions (see table 2).

**Table 2 T2:** Summary of the sessions including in AVATAR_VRSocial therapy

	Short description	Number of sessions
AVATAR therapy	Three-way dialogue between participant, avatar and therapist	Seven sessions (six sessions of + one assessment and avatar creation session)
Virtual Reality social scenarios	Interaction with social agents during quotidian situations+personalised negative voice	Three sessions

AVATAR therapy works by facilitating a novel therapeutic context in which a ‘face-to-face’ dialogue between the person and a computerised representation of their voice is facilitated by a therapist. Bespoke software transforms the therapist’s voice to match the pitch and tone of the chosen voice, and the person creates a visual representation of their voice. The voice and image are combined to produce the ‘avatar’ (ie, an animated talking virtual agent with enhanced lip-sync speech and eye blinking), through which the therapist interacts with the voice-hearer, in a three-way dialogue (for further details on the software, please see https://www.avatartherapy.co.uk/). Using this platform, the therapist can speak to the client in their normal voice or in the chosen avatar voice which is a modified version of their normal voice. Where there are multiple voices, the participant selects one to work with (usually the most dominant, frequent and distressing). The embodiment of the voice is enhanced using direct verbatim speech, and enactment of the ascribed character and background of the voice. A comprehensive account of therapeutic targets of AVATAR therapy showed that some therapeutic targets were clearly present for all therapy completers (power and control, self-esteem and future focus), whereas others (eg, maintenance processes, working with trauma, experiential disengagement) were identified in some but not all participants, in line with the tailoring of the intervention to an individualised formulation.^44^

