### Adverse events

The occurrence of AEs will be monitored actively and systematically, following guidance from the Consolidated Standards of Reporting Trials (CONSORT)^45^ with the extension for social and psychological interventions, and the extension for reporting of harms. AEs are defined as any untoward medical occurrence, unintended disease or injury, or untoward clinical signs in service user/patient participants, whether or not related to the therapy or device which require additional support or input from health professionals. AEs will be initially assessed at three levels of intensity: mild, moderate and severe, which reflect the impact of the event on the person at the time. Please note there is a distinction between ‘severe’ and ‘serious’. Seriousness is the criteria for defining regulatory reporting obligations and the following will be considered as serious adverse events (SAE, categories A–C): all deaths (category A), incidents which acutely jeopardise the health or psychological well-being of the individual, resulting in immediate hospital admission and/or permanent disability (category B) or resulting in injury requiring immediate medical attention (category C).

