In any case of an SAE, the CI must be notified within one working day by a member of the trial team becoming aware of the event. The CI (or a clinically qualified delegate) will review all SAE reports received. The CI will keep investigators informed of any safety issues that arise during the course of the trial. The CI is responsible for reporting fatal and life-threatening serious adverse reactions to the competent authorities within 7 days of the CI becoming aware of the event. The TSC will be informed of serious adverse reactions periodically. The chair of the TSC will determine the relatedness of the event to the research assessment, therapy or device based on a temporal relationship, and consideration of whether there were insufficient or inadequate instructions for use, deployment, installation or operation, or any malfunction of the AVATAR software. An AE may also be device-related if it was the result of user error or intentional misuse of AVATAR therapy software. As detailed in the risk analysis conducted for the CE-marking of AVATAR therapy software, we do not anticipate any serious adverse device effects. We do not anticipate any serious therapy or assessment-related AEs; this expectation is based on the safety data from the previous AVATAR trials.^17 19^ Reasons for withdrawal from the study will be recorded. For the final reports of the trial, the numbers, types and severity of AEs by trial condition, as well as discontinuations, will be reported using descriptive statistics.

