Clinical outcomes will be described using the mean (SD) or median (IQR) depending on the distribution of the measure and by the number (percentage) for binary outcomes. At baseline, participants will be reported overall and by randomised group. At follow-up points, participant outcomes will be presented by randomised group and the difference between groups and 95% CI for the difference will be reported to aid sample size calculations for the definitive trial. Outcomes will be reported for all randomised participants by randomised group, irrespective of whether they received the intervention or not (intention-to-treat). AEs will be reported for all randomised participants. Every effort will be made to follow-up with all participants for research assessments, and the analysis will use, where appropriate, statistical techniques for handling missing data. All analysis will be conducted in the latest version of R statistical package.

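### By-arm adverse event counts may be inflated in the therapy arm, because only that arm has up to ten extra trial contacts and the article's stated AE-form trigger at therapy discontinuation

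*Protocol article*

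**What the plan says.** All references are to the protocol article.

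- **Objectives, Table 1.** One measure of the primary objective is "Number of adverse serious and non-serious adverse events in each condition".
- **Adverse events.** In the final reports, "the numbers, types and severity of AEs by trial condition, as well as discontinuations, will be reported using descriptive statistics". No split by how or where an event came to light is given. Monitoring is promised in general terms: "The occurrence of AEs will be monitored actively and systematically". An event counts "whether or not related to the therapy or device which require additional support or input from health professionals".
- **Analysis.** "AEs will be reported for all randomised participants".
- **Trial design and flow chart.** Both arms are assessed at baseline, 3 months (T2, post-treatment) and 6 months (T3).
- **AVATAR_VRSocial.** "Therefore, this therapy consists of a total of 10 sessions": seven AVATAR sessions, including the assessment and avatar-creation session, and three VR sessions.
- **Assessments.** In the therapy arm, "Voice activity and content in the past week is monitored at the beginning of each session".
- **Exclusion criteria, withdrawal paragraph.** If therapy is stopped because the clinician links it to a marked deterioration, an AE form is to be filled in.
- **Treatment as usual.** Usual care includes monitoring by mental health services. Its amount varies and is not quantified.

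**The concern.** A count of recorded events reflects both how often events happen and how often someone is in a position to note them. Here the second factor differs between the arms by design. The therapy arm meets a trial clinician at up to ten extra points and is asked each time about the past week's voices. It also has a stated prompt for an AE form with no usual-care counterpart, since usual care has no trial therapy to stop.

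The AE definition adds a second route. It depends on input from health professionals, and the trial therapist is one more professional, in one arm only, who could give or prompt that input.

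At stake is how a primary-objective measure is read. Two columns of counts side by side invite a comparison even without a test. With 20 per arm, a few extra recorded events change the impression, and nothing in the planned table would help a reader separate detection from harm.

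**Working it through.** The article gives no AE rate and no capture probability, so there is no figure of its own to reproduce. The contact counts come from the document. The capture rates below are assumptions.

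**Step 1: scheduled trial contacts after randomisation.**
- Usual care: T2 + T3 = 2.
- Therapy: T2 + T3 + 10 sessions = 12. Counting only active sessions, as in Table 1's exposure definition ("attended at least five of nine therapy sessions"), gives 2 + 9 = 11.

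**Step 2: timing.** T2 at 3 months is post-treatment, so sessions fall in the first 3 of 6 months. From T2 to T3 the scheduled trial contact is the same in both arms. Extra capture can therefore act on about half of the events, if events are spread evenly over time (assumption).

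**Step 3: illustration with no true difference.** Assume one true non-serious event per participant, 20 participants per arm, recall *q* at the common assessments, and 80% capture in the therapy arm during the therapy period.
- *q* = 40%. Usual care: 20 × 0.40 = 8. Therapy: 10 × 0.80 + 10 × 0.40 = 8 + 4 = 12. Ratio 12/8 = 1.50.
- *q* = 60%. Usual care: 20 × 0.60 = 12. Therapy: 10 × 0.80 + 10 × 0.60 = 8 + 6 = 14. Ratio 14/12 = 1.17.

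**Step 4: range.** Let *s* be the probability that the sessions add the capture of an event in the therapy period which the assessments miss. Then

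ratio = [0.5*q* + 0.5(1 − (1 − *q*)(1 − *s*))] / *q*.

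| *q* | ratio for *s* = 0.2 to 1.0 |
|---|---|
| 0.5 | 1.10 to 1.50 |
| 0.7 | 1.04 to 1.21 |
| 0.9 | 1.01 to 1.06 |
| 1.0 | 1.00 |

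With *s* = 0 the ratio is 1.00 for every *q*. A middle case, *q* = 0.7 and *s* = 0.5, gives 14.0 recorded events under usual care and 15.5 with therapy.

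**Step 5: what a T2/T3-only table would show.** If recall at the common visits is the same in both arms, the Step 3 cases become 8 versus 8 and 12 versus 12. The excess, 12 − 8 = 4 or 14 − 12 = 2 events, appears in the separate listing for the therapy arm.

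**The case against.** The strongest reply is that the mechanism is not written down. No sentence says that AEs are elicited at therapy sessions, or that the arms are asked differently. The session opener covers selected voice items and is not described as an AE enquiry. Monitoring is promised as active and systematic, in line with the CONSORT harms extension and without restriction to one arm. Events that need extra professional input are likely to leave a trace in either arm, and a scheduled therapy session is not obviously extra input. Reporting is descriptive, with no test or ratio for AEs, and the progression criteria that the article names (recruitment, retention, uptake) include none based on AEs. The article also condenses a fuller protocol, which may hold the AE collection schedule.

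Much of this stands. It rules out saying that the therapy *will* look more harmful, and it means that the size of any bias cannot be derived from the document. It does not remove the point. The extra sessions and the AE-form prompt at discontinuation are stated in the article, so the imbalance does not rest on silence about the schedule. A promise of systematic monitoring does not say that enquiry is equal. Usual-care monitoring does not balance the sessions either: therapy is added to usual care, so that monitoring continues in both arms.

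**Conclusion.** The concern holds as a risk to interpretation. Opportunities to record AEs are unequal by design, the direction of any resulting distortion is against the therapy, and the planned by-arm table has no stated feature that would reveal it. The size is unknown and may be nil. Under the assumed rates in the working it is 8 versus 12 or 12 versus 14 recorded events. These figures rest on equal true rates, one event per participant and an even spread of events over six months.

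Two stronger readings are tempting and are not supported.

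- **A doubling of the count.** A reader might apply 80% capture to the whole follow-up and infer 8 versus 16. With 40% recall after T2 this needs 0.5*x* + 0.5 × 0.40 = 0.80, so *x* = 1.20, that is, 120% capture during therapy. Even perfect capture during therapy gives only (0.5 + 0.2)/0.4 = 1.75.
- **A trial unable to answer its safety question.** A reader might infer this from the imbalance. AE reporting is descriptive and no AE-based progression rule is stated. The categories defined as serious (death, immediate admission or permanent disability, injury needing immediate attention) are the events least likely to depend on how often a participant is seen.

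**What to change.** In the Adverse events section:

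1. Ask the same fixed AE questions in both arms at T2 and T3, after the outcome ratings. Log any disclosure of allocation as a breach under Randomisation and blinding.
2. Add a field to the AE form for the source of each report.
3. Present the by-arm AE table twice: for all events, and for events elicited by the fixed questions at T2/T3, which is the like-for-like comparison. An event already noted at a session and reported again at T2 or T3 should count in the second table. Dropping it would undercount the therapy arm.
4. Show events first noted at therapy sessions separately, for the therapy arm.
5. Keep reporting serious AEs from any source for both arms.

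The cost is a few questions at two existing visits, one form field and one more table. The like-for-like table leaves out some session-detected events, but these remain in the all-events table and the separate listing. Asking after the ratings protects that visit only. A disclosure at T2 could still unblind the same assessor for T3, because reassignment is promised only where it is operationally possible. Earlier discussion in sessions could also sharpen recall at T2, so the second table reduces the imbalance but may not remove it entirely.

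The Trial status section plans data collection until September 2026, so the questions can apply at the remaining visits in both arms. For forms already completed, the source can be filled in where the reporter is identifiable.

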### Data handling

The CI will act as custodian for the trial data. Data handling is informed by guidelines from the *Deutsche Gesellschaft für Psychologie* (German Psychological Society), the subject-specific guidelines (‘Data Management in Psychological Science’)^46^ and the European Union General Data Protection Regulation. Participants’ data will be pseudoanonymised and stored on a password-protected computer. All trial data will be stored in line with the Data Protection Act and archived in line with sponsor requirements. Data from the assessments will be entered into a central record by research workers using a secure network connection. Audio files named with a unique participant identifier will be stored as computer files on secure RUB servers. Data management will be supported by the trial statistician from MHRTC and Bochum staff and resources (ie, computerised recall centre facility). Additionally, the data will be stored on archive servers of the department of IT Services of RUB. Data will be stored for at least 10 years, and the data protection officer of RUB will supervise the storage of the data and ensure the privacy protection of the individual data subsets. Issues relating to confidentiality will be addressed and potential participants will be advised of the limits of confidentiality (ie, that the researcher will have a duty to inform health professionals if the participant discloses information which highlights any safeguarding or risk issues). All personal data will be kept in a locked filing cabinet in a locked office at the trial site and will be accessible only by researchers. Therapy files will be kept in a secure office and are not accessible to the staff collecting the research outcome data.

### Analysis

A sample size of n=20 per randomised group (n=40) will be sufficient to estimate a recruitment rate of 50% with a 95% CI of 34.51% to 65.9% and a retention rate of 80% with a 95% CI of 67.6% to 94.4% (PASS Software 2019). This sample size of 20 per arm will be sufficient to estimate the variability of the primary outcome measure (ie, changes in PSYRATS-AH and O-AS at post-treatment) for future sample size calculations, with 12 per arm sufficient for estimation of the variability for the purpose of sample size calculations.^47^ Difference between groups and 95% CI for the difference will be reported to aid sample size calculations for a definitive trial.

A complete statistical analysis will be drafted prior to recruitment beginning and finalised before any analysis is conducted. There will not be interim analyses or formal stopping rules in relation to this study as the primary goal is to establish feasibility parameters for a definitive trial. Data will be reported in accordance with the CONSORT principles, with the 2018 extension for reporting social and psychological intervention trials.^45^ We note recent CONSORT-SPI guidance, which recommends minimising the distinction between primary and secondary outcomes; therefore, all outcomes will be reported at the end of the trial.^48^ The feasibility data analysis and quantitative data analysis will be carried out by the MHRCT senior statistician clinical trials unit statistician and quality checked by a trial statistician.

Descriptive statistics will be used to summarise feasibility measures (ie, recruitment and retention, uptake of treatment, data completion) overall and by allocated group. Based on the ‘traffic light system/STOP-AMEND-GO’,^49^ progression criteria related to key feasibility outcomes such as recruitment, retention and treatment uptake rates have been proposed. Each criterion has ‘stop/amend/go’ indicators. For example, the progression criterion for treatment uptake will be 75% and above indicates the progression criterion has been met, 51–75% indicates the need to amend and below 50% indicates stop.

Clinical outcomes will be described using the mean (SD) or median (IQR) depending on the distribution of the measure and by the number (percentage) for binary outcomes. At baseline, participants will be reported overall and by randomised group. At follow-up points, participant outcomes will be presented by randomised group and the difference between groups and 95% CI for the difference will be reported to aid sample size calculations for the definitive trial. Outcomes will be reported for all randomised participants by randomised group, irrespective of whether they received the intervention or not (intention-to-treat). AEs will be reported for all randomised participants. Every effort will be made to follow-up with all participants for research assessments, and the analysis will use, where appropriate, statistical techniques for handling missing data. All analysis will be conducted in the latest version of R statistical package.

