**Methods and analysis:**

A randomised controlled feasibility trial will be conducted. 40 patients aged 18 or above who are at early stages of psychosis (first episode of psychosis in the last five years) and report distressing and interfering voices will be recruited. Participants will be randomised to receive either a novel, enhanced version of AVATAR therapy (AVATAR_VRSocial) in addition to usual care or usual care alone. Assessor-blinded assessments will be conducted at baseline, 3 months (post-intervention) and 6 months (follow­-up). Key therapeutic targets of AVATAR_VRSocial will be those established by the previous evidence of this approach (ie, power and control, self-esteem and future focus), while introducing exposure and management of distressing voices during social interactions. Analyses will focus on feasibility outcomes (recruitment, retention and completion rates) and preliminary estimates of intervention effects. Qualitative interviews will be carried out with participants allocated to AVATAR_VRSocial to gain a comprehensive understanding of participants’ views on the acceptability of the intervention and research procedures. Thematic analysis of the qualitative interviews will assess the acceptability of the intervention, trial procedures and the new VR technology and software involved.

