### Randomisation and blinding

Eligible participants will be randomised after consenting to the study and completion of the baseline assessment. Allocation will follow 1:1 block randomisation, carried out by the study coordinator, using a validated online tool (https://www.sealedenvelope.com/). The study coordinator will be unblinded to treatment allocation and will inform participants of the outcome of the randomisation. Research workers who lead the baseline and follow-up assessments will be blinded to group allocation, but participants and therapists delivering the therapy will not be (it is not possible to blind them to whether the therapy is delivered or received). Participants will be reminded not to discuss their allocation with research workers when they meet them for the assessment. Breaches in blindness will be monitored and recorded and where operationally feasible assessments will be allocated to another (blinded) research worker.

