### Participants

The study participants will be 40 people (aged 16 and above) with distressing voices and at early stages of psychosis (FEP 5 years). All research activities (including coordination of recruitment) will be based at the Mental Health Research and Treatment Centre (MHRCT), Ruhr-Universität Bochum, located in North Rhine-Westphalia region (Germany). The primary recruitment pathway will be referrals by medical professionals. Medical service centres, outpatient departments and private practitioners will be contacted for the purpose of recruitment and will act as patient identification centres. Potential participants whose mental health practitioner confirms that they experience distressing auditory hallucinations will be contacted by a member of their clinical team inviting them to learn more about the study. If a participant indicates interest, they will be contacted by a research worker who will confirm eligibility criteria and obtain consent to participate in the research. Potential participants will be offered the opportunity to discuss the study and at least 24 hours to decide whether to participate. The research worker will also assess capacity to provide consent to participate. Informative flyers will also be distributed in practices, which contain information for potential participants. Although the flyer asks participants to approach the research staff via their clinical team, previous experience shows that some will make a direct approach.^17 25^ Further self-referrals are possible because of interest generated through media/public engagement events or through the study website.

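### The precision statement for n=40 prints two upper confidence limits that do not reproduce, and its recruitment interval appears to use the 40 recruited as its denominator (minor; n=40 is not undermined)

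*Protocol article*

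**What the plan says.** In the protocol article, under Analysis, the sample size is introduced with "A sample size of n=20 per randomised group (n=40) will be sufficient to estimate" two rates. The first is "a recruitment rate of 50% with a 95% CI of 34.51% to 65.9"; the second is "a retention rate of 80% with a 95% CI of 67.6% to 94.4" (all limits in per cent). PASS 2019 is cited. No interval method is named, and no denominator other than the 40 is given for either rate. The same paragraph adds a second justification, which concerns estimating outcome variability, with 12 per arm described as enough.

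Other sections fix who the 40 are. Participants states: "The study participants will be 40 people". The abstract says that 40 patients who "report distressing and interfering voices will be recruited". Under Randomisation and blinding, "Allocation will follow 1:1 block randomisation", which agrees with 20 per arm. Table 1, under Objectives, counts patients referred, consented, declined and retained, so the pool behind a recruitment rate is larger than the group that consents.

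**The concern.** Two things look wrong. First, the printed intervals are lopsided in a way that standard intervals are not. At 50% a standard interval is symmetric, yet the printed one runs 15.49 points down and 15.9 points up. At 80% it runs 12.4 points down and 14.4 points up, whereas the usual intervals are either symmetric or reach further down.

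Second, the recruitment rate is tied to the 40 randomised. Everyone in that group has been recruited by definition, so a 50% recruitment rate cannot have them as its denominator.

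Feasibility is the primary objective, and this sentence is the only precision argument for n=40 on that objective. Anyone planning the definitive trial from these figures would carry forward an interval that cannot be reproduced and another calculated on the wrong group.

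**Working it through.** **Inputs.** n = 40, recruitment rate 50%, retention rate 80%, 95% two-sided limits (z = 1.96), all from Analysis. The 40 are the people recruited (abstract and Participants).

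**Step 1: reproduce the printed intervals.** Wald: p ± 1.96 × √(p(1−p)/n).

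- Recruitment: √(0.5 × 0.5/40) = 0.07906; × 1.96 = 0.1549. Interval 34.51% to 65.49%. Printed: 34.51% to 65.9%.
- Retention: √(0.8 × 0.2/40) = 0.06325; × 1.96 = 0.1240. Interval 67.60% to 92.40%. Printed: 67.6% to 94.4%.

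Both lower limits agree to the digits printed. The upper limits are too high by 65.9 − 65.49 = 0.41 points and 94.4 − 92.4 = 2.0 points.

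**Step 2: could another method give the printed pairs?** Results in per cent at n = 40:

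| Method | p = 50% | p = 80% |
|---|---|---|
| Printed | 34.51–65.9 | 67.6–94.4 |
| Wald | 34.51–65.49 | 67.60–92.40 |
| Wald, continuity-corrected | 33.26–66.74 | 66.35–93.65 |
| Wilson | 35.20–64.80 | 65.24–89.50 |
| Wilson, continuity-corrected | 34.06–65.94 | 63.86–90.39 |
| Exact (Clopper-Pearson) | 33.80–66.20 | 64.35–90.95 |
| Agresti-Coull | 35.20–64.80 | 64.99–89.76 |
| Jeffreys | 34.96–65.04 | 65.78–90.06 |
| t-based | 34.01–65.99 | 67.21–92.79 |
| Logit | 34.98–65.02 | 64.83–89.67 |
| Arcsine | 34.75–65.25 | 66.37–90.77 |

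No row gives either printed pair. At 80% the highest upper limit is 93.65%, so none reaches 94.4%. At 50%, an upper limit of 65.9% arises from continuity-corrected Wilson at n = 40, or from Wald at n = 38 (34.10–65.90), but neither gives 34.51%.

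**Step 3: the recruitment denominator.** Among the methods tried, and at every sample size tried (16, 20, 32, 38, 39, 40, 41 and 80), 34.51% arises only from Wald at n = 40. That points to 40 as the denominator. With that denominator, 50% means 0.5 × 40 = 20 people recruited, against a design that recruits 40.

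If 40 are recruited and the rate is 50%, the pool is 40/0.5 = 80. The article does not state this number, so it is an assumption. Then:

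- Wald: √(0.25/80) = 0.05590; × 1.96 = 0.1096. Interval 39.0% to 61.0%.
- Wilson: 39.3% to 60.7%.
- Exact: 38.6% to 61.4%.

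**Step 4: effect on width.**

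- Retention: printed 94.4 − 67.6 = 26.8 points. Wald 24.8, Wilson 24.3, exact 26.6.
- Recruitment: printed 65.9 − 34.51 = 31.4 points. Wald at n = 40, 31.0; Wald at n = 80, 21.9; exact at n = 80, 61.4 − 38.6 = 22.8.

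Each of these is narrower than printed.

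**The case against.** The best defence is that the calculation was sound and the upper limits are typing slips: 65.49 lost a digit to become 65.9, and 92.4 became 94.4. The two matching lower limits make this likely. It bears on severity, because nothing in the design, allocation or analysis depends on the slips. It does not make the printed figures right.

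It could also be said that the inputs were slightly different. A Wald interval around 81% with n = 33 does round to 67.6% to 94.4%. But almost any pair of limits can be matched if both the rate and n are free to move, and the article states 80% and n = 40.

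On recruitment, the article names no denominator, and a condensed article may leave its definition to the full protocol. That is fair, and it is why the use of 40 is put here as an inference. It does not rescue the printed interval, because the sentence presents it as what n = 40 delivers, and its lower limit comes from 40. The pool might be those referred, approached or eligible. The article does not say which the 50% refers to.

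A reader might infer that the sample size is inadequate, or that the retention precision will look worse once corrected. Neither follows. The corrected intervals are narrower, and the Wald lower limit for retention stays at 67.6%. Only a move to the exact method would lower it, to 64.4%. That is a change of method and not a correction of the slip, and the interval would still be slightly narrower than printed.

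A reader might also count the lack of an interval for treatment uptake as part of the error. The article prints no such interval, so none is wrong, and it gives the uptake thresholds only as an example of its progression criteria.

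**Conclusion.** The precision statement is wrong as written, and the matter is minor. The upper limits should be 65.49% and 92.4% on the Wald method that the lower limits identify. The discrepancies are 0.4 and 2.0 points, and they hold whatever a fuller document may contain.

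The recruitment interval appears to have been calculated on the 40 people recruited instead of the pool they were drawn from. This rests on the match of 34.51% to Wald at n = 40, since no denominator is stated. Assuming a pool of about 80, the half-width is about 11 points instead of 15.5, so the plan claims less precision than it would have.

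It would go too far to say that the trial has been planned at half its size or that n=40 lacks support. The design recruits 40 throughout, the corrected intervals are narrower than printed, and the separate argument about outcome variability is untouched.

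**What to change.** Restate the sentence on these lines: with 40 randomised participants, a retention rate of 80% would be estimated with a 95% CI of 67.6% to 92.4% (Wald, n=40); if 40 people are recruited from about 80 approached (50%), the recruitment rate would be estimated with a 95% CI of 39.0% to 61.0% (Wald). If the exact method is preferred, use it for both rates: 64.4% to 90.9% for retention (32/40) and 38.6% to 61.4% for recruitment (40/80).

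Name the interval method. Say whether the recruitment denominator is those referred, approached or eligible, and label the 80 as a planning assumption. Use the same denominator when the recruitment rate is reported and judged against its progression criterion.

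The cost is a change of wording. No participants are added, and neither the design nor the analysis changes.
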